## Abstract

**Background:**

Nowadays, metabolic syndrome has become a major health threat, and affects over one billion people globally. It also plays a great role in the growth of diseases like type 2 diabetes, coronary diseases, stroke, and other chronicity. It increases the risk of cardiovascular disorder and stroke by three to ten times and diabetic mellitus by ten times. The prevalence of metabolic syndrome is increasing globally as a result of epidemiological shift. Low and middle-income countries are facing an increasing burden of metabolic syndrome. There is a need for concerted efforts to modify behavioral risk factors that significantly contribute to the prevalence of the syndrome. This can be done by developing and implementing appropriate interventions that can bring behavior change after testing for effectiveness, feasibility, and acceptability. Thus, this study aims to develop and test the effectiveness, feasibility and acceptability of an education intervention promoting healthy lifestyle to reduce risk factors for metabolic syndrome, among office workers in Ethiopia.

**Methods and analysis:**

This randomized controlled trial will be implemented with 226 bank employees (age ≥18 years) with metabolic syndrome from government and private banks in Bahir Dar City, Ethiopia. Participants will be randomized to intervention (education) and control (general health advice) groups. The intervention group will be given one-on -one base education about healthy diets, physical exercise, stress management, avoidance of harmful alcohol consumption and smoking cessation by experts on health promotion. Text messages will be sent every two weeks and reading materials will also be provided. Additionally, a review meeting will be held at the 3^rd^ and 6^th^ month of the intervention. The primary outcomes of interest will be change in metabolic parameters (obesity levels, blood pressure, fasting blood glucose, total cholesterol, high density lipoprotein, low density lipoprotein, and triglycerides). Secondary outcomes will be knowledge, attitudes and practice of the participants towards lifestyle and cardiovascular risk factors, feasibility, acceptability, implementation fidelity, and cost-effectiveness of the intervention. Data will be collected at three time points: at baseline, at the 6^th^ month of the intervention and at the end of the intervention (9 months). Generalized linear mixed models will be utilized to compare the desired outcome between the trial arms, after accounting for baseline variations. Cost-benefit analysis and a qualitative process evaluation of the intervention will also be conducted.

**Discussion:**

This randomized control trial study will provide information on the effectiveness, feasibility, and acceptability of an education intervention promoting healthy lifestyle to reduce risk factors for metabolic syndrome, among office workers in Ethiopia, where the burden of metabolic syndrome is high among office workers.

**Clinical trial registration:**

This trial has been prospectively registered at the Australian New Zealand Clinical Trials Registry: ACTRN12623000409673p.

## Introduction

Metabolic syndrome (MetS) is a collection of disorders that comprise: obesity, insulin resistance, glucose intolerance, high blood pressure and impaired regulation of body fat [1].

World Health Organization, National Cholesterol Education Program Adult Treatment Panel (NCEP: ATP III) and International Diabetic Federation (IDF) define the condition according to the guidelines in Table 1 [2].

**Table 1 pone.0307659.t001:** Criteria for metabolic syndrome definitions in adults.

World Health Organization (WHO)	National cholesterol education program adult treatment panel (NCEP: ATP III)	International-diabetic federation (IDF)
**Insulin resistance plus two of the following:** Abdominal obesity (waist-to-hip ratio > 0.9 in men or > 0.85 in women, or body mass index (BMI) > 30 kg/m2. Triglycerides 150 mg/dl or greater, and/or high-density lipoprotein (HDL)-cholesterol < 40 mg/dl in men and < 50 mg/dl in women. Blood pressure (BP) 140/90 mmHg or greater. Microalbuminuria (urinary albumin secretion rate 20 μg/min or greater, or albumin-to-creatinine ratio 30 mg/g or greater).	**Any three or more of the following:** Waist circumference > 102 cm in men, > 88 cm in women. Triglycerides 150 mg/dl or greater. HDL-cholesterol < 40 mg/dl in men and < 50 mg/dl in women. BP 130/85 mmHg or greater. Fasting glucose 110 mg/dl or greater.	**Central obesity plus two of the following:** Triglycerides 150 mg/dl or greater. HDL-cholesterol < 40 mg/dl in men and < 50 mg/dl in women. BP 130/85 mmHg or greater. Fasting glucose 100 mg/dl or greater.

Other health care organizations each have also their own definitions that only slightly differ from the definitions of the above health care organizations [2].

Metabolic syndrome has become a major health threat in the modern world. More than one billion people in the globe are now affected by metabolic syndrome and the condition plays an important role in the blowout of the diseases like type 2 diabetes, coronary diseases, stroke, and other chronicity [3]. It increases the risk of cardiovascular disorder and stroke by three to ten times and type 2 diabetes mellitus by ten times [4]. It also raises the expense of medical care [5]. People with metabolic risk factors incur healthcare expenses that are up to 20% more than those of patients without risk factors. They use outpatient and physician services more frequently, spend more money on drugs, and require longer hospital stays [6].

Metabolic syndrome is speedily expanding in the developing world [7, 8]. Sub Saharan Africa and the Middle East / North Africa are predicted to have the highest rates of diabetes increase over the next 25 years, at 141% and 104%, respectively [3]. This indicates that, the prevalence of metabolic syndrome will also increase by more than three times in the next 25 years in the continent.

The reasons for the increase of metabolic syndrome prevalence in Africa are thought to be due to a shift from traditional African to western lifestyles or the rise in the use of risk behaviors, such as consumption of unhealthy diet, reduced physical activity, harmful alcohol consumption and tobacco use, as well as due to the increment of urbanizations and increasing life expectancies [9, 10]. Globalization has also contributed a significant impact on the incidence of metabolic syndrome in sub-Saharan Africa via contributing to the availability of unhealthy diet, the expansion of urbanization, racial and cultural tensions, political upheaval and stress over time [11]. The development of metabolic syndrome is also greatly influenced by knowledge, attitudes, and practices (KAP) towards lifestyle and cardiovascular risk factors [12–14].

The status of metabolic syndrome in Ethiopia is similar to that in Africa more broadly. It is an emerging public health issue for the nation. According to a systematic review and meta-analysis study conducted in 2020, the pooled prevalence of metabolic syndrome in Ethiopian population is 34.89% and 27.92% according to ATPIII and IDF diagnostic criterions respectively [15]. In addition to consumption of high calorie-low fiber fast food and the decrease in physical activity, one of the main factors for the increment of metabolic syndrome is prolonged sitting and stress due to work behavior in Ethiopia [16–19]. Different studies confirmed that the prevalence of metabolic syndrome among office workers is high. A cross-sectional study conducted in Ethiopia in 2019 among 1,164 adults working in office revealed that, the prevalence of metabolic syndrome was 20.1% [18]. A study conducted in Ethiopia among 1,935 bank employees and teachers also confirmed that, the overall prevalence of metabolic syndrome was 12.5% and 17.9%, according to ATPIII and IDF respectively [20]. A cross sectional study conducted on the prevalence and associated factors of undiagnosed hypertension among bank workers in Bahir Dar city, Ethiopia, also showed that, the overall prevalence of undiagnosed hypertension among 513 bank workers was 24.8% [21]. Another cross-sectional study carried out among 368 bank employees in Bahir Dar, Gondar, and Dessie, Ethiopia, also found that the prevalence of hypertension was 52.4% [19]. That means bank workers are at greater risk for metabolic syndrome due stress and prolonged sitting at work, in addition to using mechanized transportations and consumption of high Calorie-low fiber fast food.

Given this increasing burden of metabolic syndrome in Ethiopia, there is an urgent need to develop effective and appropriate interventions that can bring behavior change after testing for effectiveness, feasibility, and acceptability [22, 23]. Education interventions for healthy lifestyle have been successful in many settings [24, 25]. However, most interventions for metabolic syndrome have only been tested in middle and high -income settings. According to a prospective, longitudinal, nonequivalent pretest-posttest comparison group design study conducted in San Jose, Costa Rica and Chiapas, Mexico to evaluate the impact of education intervention for healthy lifestyle to reduce cardiovascular diseases confirmed that there was a significant improvement of behavior change in the intervention group [25]. But we do not know this will be equally effective or not in Ethiopia, and it is essential to test the specific effectiveness, feasibility and acceptability in Ethiopia. As well, the level of knowledge, attitudes and practice towards lifestyle and cardiovascular risk factors among bank workers with metabolic syndrome in Ethiopia, have not been investigated.

Thus, this study will provide evidence about the effectiveness, feasibility and acceptability of lifestyle education intervention on the metabolic syndrome, the level of knowledge, attitudes and practice towards lifestyle and cardiovascular risk factors among bank employees with metabolic syndrome in Ethiopia. Consequently, the evidence will be used for policy makers to scale up this management strategy and for stakeholders, as an input to plan effective metabolic syndrome management strategy, and will also be used as a reference for other randomized control trial study. Moreover, it will be used as evidence for professionals to apply this intervention for risky groups.

## Objectives

➢ To develop and test the effectiveness of a lifestyle education intervention on metabolic syndrome management among bank employees in Ethiopia.➢ To assess and compare the levels of knowledge, attitudes, and practices towards lifestyle and cardiovascular risk factors before and after the intervention as well as between the control and intervention groups among bank employees with metabolic syndrome in Ethiopia.➢ To assess the feasibility, and acceptability of an education intervention for healthy lifestyle on metabolic syndrome management among bank employees in Ethiopia.➢ To evaluate the cost-benefit of the educational intervention promoting healthy lifestyle to reduce risk factors for metabolic syndrome among bank employees in Ethiopia.➢ To evaluate the process of education intervention promoting healthy lifestyle to reduce risk factors for metabolic syndrome for bank employees in Ethiopia.

## Methods

### Study design

A randomized control trial using a parallel design will be employed to develop and test the effectiveness, feasibility, and acceptability of lifestyle intervention on metabolic syndrome management, and to assess and compare the levels of knowledge, attitudes, and practices towards lifestyle and cardiovascular risk factors before and after the intervention as well as between the control and intervention groups among bank employees with metabolic syndrome, and also to evaluate the cost effectiveness and the implementation process of the intervention. The trial has been designed according to the Standard Protocol Items: Recommendations for Interventional Trials (SPIRIT) (**S1 File**). It is registered with the Australian New Zealand Clinical Trials Registry (ACTRN12623000409673p).

### Study setting

The study will be conducted in the Bahir Dar city, Ethiopia, among bank workers. Bahir Dar is located 565 km Northwest of Addis Ababa and it is the capital city of the Amhara regional state. There are 210 bank branches with 2,310 workers in the city.

### Participants and recruitment

The participants of this trial will be employees of both private and government banks in Bahir Dar City, Ethiopia. Bank employees are chosen as participants in this intervention trial because studies done among bank employees in Ethiopia revealed that the prevalence of metabolic syndrome is significant and that rapid intervention is needed for this population [19–21]. For instance, a cross-sectional study conducted in Ethiopia among 1,935 bank employees and teachers found that 12.5% of participants had metabolic syndrome, and it recommended for more efforts to screen for, identify, and treat MetS and its components among Ethiopian bank employees [20]. A cross-sectional study conducted on the prevalence and contributing factors of undiagnosed hypertension among bank employees in Bahir Dar city, Ethiopia, also found that the prevalence of undiagnosed hypertension among 513 bank employees was 24.8%, and that low levels of knowledge about hypertension and physical inactivity were the main risk factors for the development of hypertension. This study suggested that creating awareness, frequent screening and apply the right interventions for this vulnerable group is crucial [21]. Another cross-sectional study done among 368 bank employees in Amhara metropolitan cities (Bahir Dar, Gondar, and Dessie) also found that the prevalence of hypertension was 52.4%, and that variables such as overweight and obesity, daily fruit consumption, moderate to vigorous physical activity, the presence of stressful events, and inadequate cardiovascular diseases knowledge were all linked to hypertension [19]. This study recommended that raising awareness about cardiovascular disorders and behavior change interventions that enhance bank workers’ engagement in physical exercise, and a healthy diet is urgently required for this group of population. The other reasons to select bank workers as participants is the fact that bank employees have a generally stable workforce and are willing to participating in the study are the other reason used to choose participants.

The following methods will be applied to contact and recruit participants: The district headquarters of each bank will get an official letter from the health department of the city administration, after which letters will be issued to each bank branch from the head office of the bank and communications will be made between the managers of each branch and the bank employees. Then, participants will be approached and recruited after being informed about the objectives of the study, inclusion and exclusion criteria, the potential benefits and risks of participation, and ethical considerations of the study. Finally, prior to the start of data collection, written informed consent will be obtained from each participant. Then, the participant will be recruited and screened based on their level of obesity and blood pressure, and those who meet at least one of the two criteria (obesity or high blood pressure) will be included in the trial and will have test for biomarkers (Fasting blood glucose level, Total cholesterol, High density lipoprotein cholesterol, low density lipoprotein cholesterol, and Triglyceride).

To make recruiting effective and to increase participant willingness, the objectives of the study, inclusion and exclusion criteria, ethical considerations of the study, the advantages of the study and their rights even to stop in the middle of the procedure will be explained to participants. The participants will be informed that their participation in this study is very important for the success of the study and for paving the way for the development of the policy in this area. Additionally, they will be told that there is no risk except some discomforts to them in taking part in this study, and that all data obtained from them would be kept confidential via a password with no requirement that their identities be recorded, and results will also be communicated to them at the end of the study. They will also be told that even if they do not meet the requirements to participate in the study, they will still get advice on living a healthy lifestyle and about seeking medical counsel if they exhibit any signs of metabolic syndrome.

### Inclusion and exclusion criteria

#### Inclusion criteria

Bank workers with age ≥18 years old and who fulfil at least one of the following National Cholesterol Education Program Adult Treatment Panel III (NCEP: ATPIII) metabolic syndrome criteria; Waist circumference >102 cm in men, > 88 cm in women, Triglycerides ≥150 mg/dl, HDL-cholesterol < 40 mg/dl in men and < 50 mg/dl in women, BP ≥130/85 mmHg, fasting glucose ≥110 mg/dl will be included in the study.

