### Dependent variables

#### Primary outcomes

*Body size (Central obesity)*. These will be defined as waist circumference > 102 cm in men, > 88 cm in women [2], and will be measured with a tape measure at the approximate midpoint between the lower margin of the last palpable rib and the top of the iliac crest or at the abdomen’s maximum extension. It will be measured at the baseline and 9^th^ month of the intervention.

*Blood pressure (BP)*. Which is defined as BP ≥ 130/85 mmHg [2, 28], and will be measured as follows: Three blood pressure measurements will be taken using appropriate size sphygmomanometer after the person is taking a rest for 5 minutes for the first measurement and with a difference of 5 minutes between successive measurements. The mean systolic and diastolic BP measurements will be considered for interpretation. The measurement will be taken at the baseline and the 9^th^ month of the intervention.

*Biochemical markers*. Fasting blood glucose (FG), high density lipoprotein (HDL), and triglycerides (TGL)) which are defined as fasting glucose ≥110 mg/dl, HDL-cholesterol < 40 mg/dl in men and < 50 mg/dl in women and Triglycerides ≥150 mg/dl respectively [2]. From each eligible individual 5 ml of venous blood will be collected at baseline and at the end of the intervention before breakfast by employing infection prevention procedures. Plasma and serum will be separated by laboratory technologist and stored at -80°C for later analyses at Bahir Dar University teaching hospital laboratory department. The tests will analyze FG, total cholesterol, HDL-C and TGL, while low-density lipoprotein will be determined indirectly.

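### Participants are described as having metabolic syndrome (three of five ATP III criteria), but the entry rules require one criterion, so conclusions about employees with the syndrome would not be supported

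*Protocol article*

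**What the plan says.** **The label.** The abstract (Methods and analysis) says the trial will enrol "226 bank employees (age ≥18 years) with metabolic syndrome from government and private banks". The closing paragraphs of the Introduction use the same label. So does the objective on knowledge, attitudes and practices (KAP), which compares outcomes "between the control and intervention groups among bank employees with metabolic syndrome in Ethiopia", and so does Study design ("between the control and intervention groups among bank employees with metabolic syndrome, and also to evaluate the cost effectiveness").

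**The definition.** Table 1 in the Introduction gives the ATP III rule as "Any three or more of the following", followed by five items: waist circumference, triglycerides, HDL, blood pressure and fasting glucose.

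**The entry rules.** Inclusion criteria admit adult bank workers "who fulfil at least one of the following National Cholesterol Education Program Adult Treatment Panel III (NCEP: ATPIII) metabolic syndrome criteria". Exclusion criteria start from the same one-criterion base. Participants and recruitment gives a different rule. Screening there uses two measures only, and the section states: "those who meet at least one of the two criteria (obesity or high blood pressure) will be included in the trial". The biomarkers are tested after that step.

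**The concern.** The label, the inclusion rule and the recruitment rule do not describe the same people. The label needs three criteria, the inclusion rule needs any one of five, and the recruitment rule needs one of two named criteria. No section requires three.

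What is at stake is whom the results concern. The Introduction says the evidence will help policy makers scale up a strategy for managing metabolic syndrome. If an unknown part of the sample has one or two risk factors only, a result reported for employees with metabolic syndrome is attached to the wrong group. Glucose, HDL and triglycerides are also primary outcomes, and entry does not select on them. Participants with normal baseline values have less room to improve on those markers; the documents give no basis for sizing that effect.

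**Working it through.** **Step 1. The rules side by side.**

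| Place in the protocol article | Requirement |
|---|---|
| Abstract, Introduction, KAP objective, Study design | metabolic syndrome |
| Table 1, ATP III column | at least 3 of 5 criteria |
| Inclusion and exclusion criteria | at least 1 of 5 |
| Participants and recruitment | obesity or high blood pressure, biomarkers tested after inclusion |

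Consequences:
- A worker with raised blood pressure only enters under both entry rules and does not have the syndrome.
- A worker whose only abnormality is triglycerides, HDL or glucose is eligible under the inclusion criteria but is not reached by the recruitment procedure.
- A worker with all three laboratory criteria and neither of the other two has the syndrome under Table 1 and is not reached either. This is the only pattern of cases missed, because any other set of three contains waist or blood pressure (taking obesity in the recruitment text to mean the waist cut-off).

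**Step 2. What share could have the syndrome?** The plan gives no figure for this, so it can only be bounded.

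Inputs: 2,310 bank workers (Study setting). From the Introduction: metabolic syndrome 12.5% by ATP III in bank employees and teachers, and 20.1% in office workers; undiagnosed hypertension 24.8% in Bahir Dar bank workers; hypertension 52.4% in bank employees in three cities.

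Cases: 2,310 × 0.125 = 289; 2,310 × 0.201 = 464.

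Pool meeting the blood pressure criterion, with hypertension prevalence as proxy: 2,310 × 0.248 = 573; 2,310 × 0.524 = 1,210.

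Upper bound on the share with the syndrome = cases ÷ pool, supposing every case is in the pool:

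| | Pool 573 | Pool 1,210 |
|---|---|---|
| 289 cases | 50% | 24% |
| 464 cases | 81% | 38% |

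Workers entering on obesity alone enlarge the pool and lower every cell. The Introduction's pooled national ATP III figure of 34.89% is not specific to office workers. It gives 2,310 × 0.3489 = 806 cases, which is 67% of 1,210 and more than the whole pool of 573, so it sets no bound there.

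**Step 3. What a three-criterion subgroup could show.** The plan's sample size reproduces: (15.0² + 16.3²) × 2.8² ÷ 6.4² = 490.69 × 7.84 ÷ 40.96 = 93.9, so 94 per arm and 188 in all; 188 × 1.2 = 225.6, so 226. Suppose, for illustration, that half of the 226 meet three criteria: 113 people, about 45 per arm after 20% attrition (113 × 0.8 ÷ 2 = 45.2). The standard error of the systolic difference is √(490.69 ÷ 45) = 3.30 and 6.4 ÷ 3.30 = 1.94. Power is about Φ(1.94 − 1.96), or 49%.

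**The case against.** The strongest reply is that the overall aim, to reduce risk factors for metabolic syndrome among office workers, suits a one-criterion population, and that only one of the five objectives says the participants have the syndrome. That is correct, and it is why rewording is a sufficient remedy. It does not remove the conflict, because the abstract, Introduction, KAP objective and Study design all carry the label.

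A second reply is that, if obesity means the waist cut-off, everyone the recruitment procedure admits also satisfies the inclusion criteria. This stands: nobody ineligible is enrolled. The procedure narrows reach, which is a matter of generalisability.

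A reader might infer three stronger things that the documents do not support:
- *That the conclusions concern a population not enrolled at all.* Some participants will meet three criteria. The sample is broader than the label and largely overlaps with it in kind.
- *That most participants will lack the syndrome, because 226 would be 78% of the 289 expected cases.* That ratio shows how hard it would be to recruit cases only. It does not give the share of cases among those admitted, and the bounds above run on both sides of one half.
- *That frozen blood proves laboratory values cannot decide entry.* Primary outcomes says samples are "stored at -80°C for later analyses at Bahir Dar University teaching hospital laboratory department", with no storage time. The inference rests on the order of steps in Participants and recruitment.

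**Conclusion.** The contradiction is in the text and needs no assumption. The sample will be a mixture, and a substantial part of it may lack metabolic syndrome. On the article's own figures the share with the syndrome is at most about 24% to 81%, depending on which prevalence and which pool are used. Those bounds assume that hypertension prevalence stands in for the 130/85 mmHg criterion, that prevalences from other samples apply to the city's 2,310 workers, and that enrolment reflects the pool. The 24.8% figure counts undiagnosed cases only, so the smaller pool is probably too small and the 81% too generous.

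A conclusion about employees with metabolic syndrome is not supported as the plan stands. The comparison between arms is not biased by this point, since both arms are entered under the same rule, and the sample size calculation is untouched. The fault lies in whom the trial can speak about.

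**What to change.** Reconcile the abstract, the Introduction, the KAP objective, Study design, Participants and recruitment, and the inclusion and exclusion criteria to one population. Recruitment was reported as begun on 20 November 2023, so the cheap way is to describe the procedure actually run: employees with central obesity and/or elevated blood pressure, at risk of metabolic syndrome. Conclusions should be limited to that population.

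Report how many participants in each arm met three or more ATP III criteria at baseline, and add an analysis of that subgroup, labelled in advance as supportive and underpowered. The metabolic parameters are already collected from both groups at baseline, so no new measurement is needed.

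The cost is wording in those places, one descriptive count and one supportive analysis. The downside is a narrower claim.
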